#### Microbiological studies:

**At all participating centers:** standard microbiological methods will be used, following SEIMC recommendations for the diagnosis of bacteremia (<http://www.seimc.org/documentos/protocolos/microbiologia>). For sensitivity testing, EUCAST guidelines will be followed.

**Studies to meet Objective 5 (100 isolates selected at HUVM and HUVV):** 1. Identification: Isolates will be identified by MALDI-TOF.

2. Sensitivity testing: The sensitivity of the 100 *S.aureus* isolates to the following antimicrobials will be tested by broth microdilution: penicillin, amoxicillin/clavulanic acid, oxacillin, gentamicin, tobramycin, amikacin, ciprofloxacin, levofloxacin, erythromycin, clindamycin, tetracycline, trimethoprim/sulfamethoxazole, linezolid, teicoplanin, vancomycin and daptomycin, following the EUCAST methodology.

3. Mass sequencing: Extraction of DNA from isolates will be performed using a Qiacube automatic extractor (Qiagen). The highly sensitive Qubit system (Thermo Fisher Scientific) will be used for fluorimetric quantification of extracted DNA. Enzymatic fragmentation of the DNA, addition of adapters and indexes, PCR amplification and subsequent clean-up, and library normalization will be performed according to the manufacturer's instructions (Nextera DNA Flex library prep kits [Illumina]). Library quality will be checked on the

Agilent 2100 Bioanalyzer system using a high-sensitivity chip. Library mixing and sequencing will be performed on a MiSeq sequencer (Illumina), using the Illumina MiSeq v3 reagent kit (600 cycles and 2x300 paired-end reads). Reads will be quality-filtered and assembled with CLC Genomic Workbench v10 (Qiagen) software. The RAST server will be used for gene annotation. FastQ files generated for each sample will be used for genotyping and identifying genes of interest (ResFinder and VirulenceFinder of the Center for Genomic Epidemiology CGE], <http://www.genomicepidemiology.org/>). These databases will also be used to establish clonal relatedness between strains using multilocus sequence typing (MLST finder).

**OTHER METHODS** (100 patients sorted by different phenotypes, from HUVm and HUVV):

Study of dysregulated cytokine production: Blood samples from 100 patients will be tested to determine differences between the phenotypes for the main markers of cytokine dysregulation. Cytokine and adhesion molecule levels will be determined by Bio-Plex assay. EDTA tubes will be used for the collected samples. Blood samples will be centrifuged for 15 min at 1000 g, aliquoted into 0.2 mL tubes, and stored at -80°C until analysis. For each sample, the Bio-Plex multiplex immunoassay will be used to simultaneously quantify (working in microplates) up to 12 human cytokines. The cytokines to be analyzed will be chosen from among the following: basic FGF, eotaxin, G-CSF, GM-CSF, IFN- $\gamma$ , IL-1 $\beta$ , IL-1ra, IL-1 $\alpha$ , IL-2R $\alpha$ , IL-3, IL-12 (p40), IL-16, IL-2, IL-4, IL-5, IL-6, IL-7, IL-8, IL-9, GRO- $\alpha$ , HGF, IFN- $\alpha$ 2, LIF, MCP-3, IL-10, IL-12 (p70), IL-13, IL-15, IL-17A, IP-10, MCP-1 (MCAF), MIG,  $\beta$ -NGF, SCF, SCGF- $\beta$ , and SDF-1 $\alpha$ .

Study of markers of endothelial dysfunction: Differences in the main markers of endothelial dysfunction (plasma levels of E-selectin, VCAM-1 and ICAM-1) in the 100 representative samples. For determination of adhesion molecule levels, EDTA and heparin plasma samples (for measurement of E-selectin) will be collected and centrifuged within 30 minutes of blood collection. Subsequent aliquots will be stored at -80°C until analysis: E-selectin, VCAM-1 and ICAM-1 levels will be assessed with commercially available ELISA kits and a photometer (Tecan Sunrise, Craisheim, Germany) measured at 450 nm.

Immunological study: quantification of immunosuppression by flow cytometry: Whole blood drawn into K3-EDTA collection tubes will be used for flow cytometry analysis (BD FACS Canto II) of different subpopulations. For analysis of the main lymphocyte subpopulations (LT, LB, NK, CD4, CD8), a 6-color antibody panel (for CD45, CD3, CD4, CD8, CD16+56, CD19) will be used, and for Treg lymphocytes, a 3-color antibody panel (CD4, CD25 and CD127). Analyses of activated CD4 and CD8 lymphocytes: OX40+, HLA-DR+, CD28, inhibited lymphocytes (PD-1, CTLA-4), and myeloid-derived suppressor cells (MDSC) with simultaneous

labelling of CD45, CD33, CD11b, HLA-DR, CD14 and CD15. Dendritic cells: Lin- CD45 + CD11c- CD11b + CD123 + HLA-ABChigh HLA-DRhigh CCR7high OX40L + DC-SIGN + CD86highCD80highCD40highCD83+.

Genetic study of the patients: Whole blood samples will be taken from each patient. These samples will be immediately frozen at -80°C and then sent to the Hospital Universitario de Valme where they will be cryopreserved awaiting genetic analysis. DNA will be isolated from frozen whole blood samples using the Qiacube system (Qiagen, Hilden, Germany) according to the manufacturer's instructions, and its concentration measured by fluorimetry, using the Qubit 3 fluorometer (Thermo Scientific, Wilmington, USA). Candidate gene variants identified in the literature will be analyzed using the AriaMX system (Agilent Technologies, Santa Clara, USA) and Taqman probes. Quality controls for genotyping and genetic association studies will be performed as previously described (Real LM, et al. A polymorphism linked to RRAS, SCAF1, IRF3 and BCL2L12 genes is associated with cirrhosis in hepatitis C virus carriers. Liver Int 2014; 34:558-66).

## **7. Data management.**

Data will be collected in the electronic DCN online. Each participating center will be assigned a key and password to access the electronic DCN online and enter the data / variables required for each case. DCNs will be numbered with a code to ensure sample and data confidentiality.

## **8. Data analysis.**

ISAC Cohort: Objectives 1 and 2: Missing value analysis and imputation, if applicable, will be performed using standard techniques. To derive the phenotypes, a two-step cluster analysis with silhouette analysis will be performed on a randomly selected subcohort including two-thirds of the patients. The phenotypes will be represented as chord diagrams and heat maps. The distribution of phenotypes and characteristics will be validated on the other subcohort with one-third of the patients. Multivariate analysis (Cox or logistic regression) will be performed to control for the effects of antibiotic treatment and control of focus of infection on the association between the identified phenotypes and the outcome variable. Objective 3: A binary (if two phenotypes are obtained) or multinomial (if >2) logistic regression model will be used to predict the phenotypes obtained. A simplified probabilistic model of phenotype assignment will then be developed based on the final logistic regression model selected.

Prospective cohort: (Objective 4). Each patient with SAB will be assigned a phenotype that will be calculated on the basis of the simplified probabilistic model. Mortality rates (at 30 days and six months), persistent bacteremia and complicated bacteremia will be compared between the different types of phenotypes. Multivariate analyses (Cox or logistic regression) will be calculated to control for the effect of other covariates

(such as treatment administered or source control) on the association between identified phenotypes and outcome variables.

Study of genetic, immunological, biochemical and microbiological variables in representative patients with different phenotypes, randomly selected from the prospective cohort of HUVVM and HUVV cases (Objective 5):

Differences in frequencies or medians of the data for genetic virulence factors, biomarkers or immunological factors across the different phenotypes will be analyzed by the chi-square or Mann-Whitney U test and multivariate logistic regression models, taking into account possible confounding variables.

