## 7. Primary objective.

To determine retrospectively whether different clinical phenotypes exist among patients (adults and children) who develop *Staphylococcus aureus* bacteremia.

Secondary objectives:

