The approach outlined in this research project proposal is based on the hypothesis that patients who develop *S. aureus* bacteremia could be categorized into a few clinical patterns (phenotypes) based on demographic characteristics, comorbidities, history, signs, symptoms, and laboratory tests at presentation. Such phenotypes, if they exist, could be indicative of different physiopathological mechanisms, as well as be associated with a better or worse prognosis. They could help to better identify patients with *S. aureus* bacteremia at higher risk of complications and those who are not, which could improve treatment strategies and patient follow-up, resulting in a reduction in mortality and complications associated with this type of infection. In addition, the analysis of possible genetic, immunological and pathophysiological mechanisms that would explain the clinical presentation of bacteremia according to the phenotypes identified would lead to the investigation of new treatment strategies. Consequently, our proposal for this Research Project also includes a study of phenotypes associated with a higher or lower risk of developing complications and mortality, and an analysis of their differences based on genetics, microbiology (presence of virulence genes), immunological and physiopathological factors such as endothelial dysfunction (early biomarkers of endothelial dysfunction) and cytokine dysregulation.

Given the particular characteristics of the pediatric population, a specific subanalysis of this population is also foreseen. The Andalusian pediatric infectology and immunopathology group will contribute to the project for this part of the project.

Presentation according to different clinical phenotypes has been described in different pathologies but never in *S. aureus* bacteremia. For example, one study identified clinical phenotypes among patients with sepsis (Seymour et al. JAMA 2019). Our group also recently identified three clinical phenotypes associated with prognosis in patients with COVID-19 requiring hospital admission (Gutierrez-Gutierrez et al, Lancet Infect Dis 2021). It is considered that this approach to the study of such a serious pathology could be of great utility for the clinical management of patients (both in the adult and pediatric populations) and its results of great interest to the medical and scientific community.

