## 5. Expected sample size and basis for determination.

For the retrospective study (objectives 1-3) based on the ISAC database: we estimate that we will be able to analyze at least 1,800 cases of SAB that meet the inclusion criteria. For objective 4: we estimate prospective inclusion of 1000 cases from the 14 participating centers during 34 months of follow-up.

For objective 5: we estimate that 3 or 4 phenotypes will be identified, and therefore that 100 patients/isolate will be sufficient to provide 25-33 patients per phenotype, which will allow a reasonable number of cases for comparison of microbiological, genetic, endothelial and immunological parameters.

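### The primary question is whether phenotypes exist, but the analysis plan states no rule by which it could conclude that they do not

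*Combined protocol and SAP*

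**What the plan says.** Protocol section 7 (Primary objective) sets an existence question: "To determine retrospectively whether different clinical phenotypes exist among patients (adults and children) who develop" S. aureus bacteraemia. The objectives section repeats it, and the literature review words the hypothesis conditionally: "Such phenotypes, if they exist, could be indicative of different physiopathological mechanisms".

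Methods section 8 (Data analysis) gives the whole derivation in one clause: "a two-step cluster analysis with silhouette analysis will be performed on a randomly selected subcohort including two-thirds of the patients". Validation is described as follows: "The distribution of phenotypes and characteristics will be validated on the other subcohort with one-third of the patients". The next step is the assignment model: "A binary (if two phenotypes are obtained) or multinomial (if >2) logistic regression model will be used to predict the phenotypes obtained".

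Methods section 5 expects "we will be able to analyze at least 1,800 cases of SAB that meet the inclusion criteria". It plans the 100-patient substudy on the basis that "we estimate that 3 or 4 phenotypes will be identified", so that 100 "will be sufficient to provide 25-33 patients per phenotype".

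The plan gives no range for the number of groups (k), information criterion, minimum silhouette, reference distribution, measure of agreement or definition of failed validation. The limitations section (Methods section 10) does not mention the matter.

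**The concern.** A question that begins with whether needs a result that would count as no. Section 8 has no such result. The silhouette compares each patient's own group with the nearest other group, so it needs at least two. The modelling branch starts at two. The validation step can be described but cannot fail.

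The risk is that one population with a continuous severity gradient is cut into groups and reported as phenotypes. Secondary objectives 1 to 4 (prognosis, assignment model, prospective validation, mechanistic substudy) all build on the groups. A link with mortality would be no safeguard, because a severity gradient cut in two would also predict death.

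**Working it through.** **Figures in the plan.** The only stated figure that depends on the number of groups is the substudy size: 100/4 = 25 and 100/3 = 33.3, which reproduces 25-33. It presupposes three or four phenotypes. The existence question itself has no figure. With 1,800 patients, derivation uses 1,800 × 2/3 = 1,200 and validation 600.

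**Silhouette at k = 1.** For each patient s = (b − a)/max(a, b), where a is the mean distance to patients in the same group and b is the smallest mean distance to another group. With one group b does not exist and s is undefined. A maximum taken over k must therefore be taken over k ≥ 2 and always returns at least two. This is a matter of definition and needs no simulation.

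**Does the size of the silhouette, or an information criterion, settle existence?** Simulation: n = 1,200, 20 data sets per scenario, k-means as a stand-in for two-step clustering, k up to 6. Not from the documents: normally distributed inputs, their number, and the correlations and shifts.

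| Scenario | k by silhouette | Mean maximum silhouette | k by classification-mixture BIC (k = 1 allowed) |
|---|---|---|---|
| One population, 10 independent variables | 2 in 20/20 | 0.072 | 1 in 20/20 |
| One population, 30 independent variables | 2 in 20/20 | 0.027 | 1 in 20/20 |
| One population, gradient, correlation 0.3 (10 variables) | 2 in 20/20 | 0.194 | 2 in 7, 3 in 13 |
| One population, gradient, correlation 0.5 (10 variables) | 2 in 20/20 | 0.274 | 4 in 20/20 |
| Three real groups, each shifted 4 SD on its own variable (10 variables) | 3 in 20/20 | 0.352 | 3 in 20/20 |
| Three real groups, each shifted 2 SD on its own variable (10 variables) | 3 in 20/20 | 0.138 | 1 in 20/20 |

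A single gradient reached a mean silhouette of 0.274, above the 0.138 from three real but modest groups, so an uncalibrated value cannot decide. The BIC recognised unstructured data, but it split the gradients and missed the modest groups. A two-step-type BIC on the same k-means partitions never returned one group.

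**Does the held-out third reveal a false split?** Simulation: n = 2,128 (370 + 88 + 498 + 75 + 403 + 694, from Tables S3-S5), two-thirds for derivation (1,419), 30 mixed continuous and binary inputs, one common factor and no groups. It was repeated with different code and scaling, at 12 to 40 data sets per setting. Median adjusted Rand index between the derived split and the held-out third, as a range over the repeats:

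- loading 0: 0.02 to 0.05
- loading 0.15: 0.03 to 0.34
- loading 0.30: 0.69 to 0.79
- loading 0.45: 0.87 to 0.90; where the chosen k was recorded, two groups were chosen in 39/40 and 20/20 data sets

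Replication therefore exposes a false split when structure is absent or weak, and not when the gradient is moderate to strong. The loadings are assumptions; the documents give no correlations.

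**The case against.** The best defence is that section 8 does not say that the silhouette selects the number of groups. Two-step clustering may use an information criterion that is defined at k = 1, with the silhouette only describing quality. A very low silhouette, or poor agreement in the remaining third, could also be read as evidence against phenotypes. This stands as far as it goes: a reader might infer that the method can only answer yes, and the text does not support that. It does not close the gap. The criterion is not stated, a BIC that admits one group still split a gradient, and neither a low silhouette nor poor agreement has a threshold.

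A reader might also infer that reproducibility can never reveal the error. The simulations contradict this at loadings of 0 to 0.15.

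A third tempting inference is that Tables S3-S5 already show a severity gradient cut in half, because sub-phenotype 2 has more hypotension and inotrope use. The tables do not support it:

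- Sub-phenotype 2 is 88/458 (19%), 75/573 (13%) and 694/1,097 (63%) of A, B and C. At loading 0.45 the simulated smaller group was 41 to 49%.
- The hypotension contrast in C has p = 0.06.
- B2 has lower creatinine (0.96 v 1.21 mg/dL) and less haemodialysis (17.3 v 24.3%).
- C1 has more native valve (11.7 v 5.0%), vertebral (16.6 v 2.9%) and deep tissue or abscess (17.1 v 4.5%) infection.
- In Table S7 the clusters follow portal of entry in 286 + 431 + 409 = 1,126 of 1,217 patients (92.5%), which is not a two-way severity cut.

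The tables neither prove nor exclude a gradient, and they supply no decision rule.

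**Conclusion.** The concern holds as a gap in the decision rule for the primary objective. The plan pre-specifies no way to conclude that phenotypes are absent. If k is chosen by silhouette, two or more groups are certain whatever the data; whether k is so chosen is not stated. The size of the risk depends on how strongly the inputs share a common gradient, which the documents do not report. At assumed loadings of about 0.30 to 0.45 a false split would also pass an informal replication check; at 0 to 0.15 it would not. The simulated figures rest on k-means in place of the two-step algorithm and on assumed inputs. The missing rule and the behaviour of the silhouette at k = 1 rest on neither. Nothing here shows that the reported phenotypes are false.

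**What to change.** In Methods section 8:

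1. State the criterion that selects the number of groups, and a range of k that includes 1.
2. Compare the observed silhouette (or the gap statistic, which admits k = 1) with data sets simulated from a single population that keeps the ISAC margins and correlations. One workable choice is 200 Gaussian-copula sets, accepting two or more phenotypes only above the reference 95th percentile. Other calibrated references would also serve. Adding k = 1 without a reference is not enough.
3. Set an agreement measure and threshold for the one-third validation, for example a minimum adjusted Rand index.
4. Apply the same rule to any sub-phenotype split. Section 8 plans none, but the appendix reports one.
5. State what follows if the rule is not met: report a continuous score and say that distinct phenotypes were not shown.

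The cost is SAP wording and some computing, with no new data, and the possibility of a negative answer. Because the appendix already reports derived groups, a check made now should be labelled as added after derivation.

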### Secondary objectives:

- 1 To evaluate the reproducibility of these clinical phenotypes and their correlation with mortality (30 days and 6 months)
- 2 To derive and validate a simplified probabilistic model of phenotype assignment.
- 3 External validation of the simplified probabilistic model of clinical phenotype assignment in a prospective cohort, and determination of associations with mortality and the development of complicated bacteremia within 6 months.
- 4 To apply microbiological (clonality testing, genome sequencing), biochemical and immunological techniques to elucidate the pathophysiological and genetic mechanisms underlying the phenotypes.

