## 8. Design.

This is an entirely observational study.

Primary Objective and Secondary Objectives 1 and 2: The ISAC cohort will be analyzed. This cohort is the result of an international study (11 hospitals in 5 countries) on bacteremia caused by *S.aureus* (2,590 cases collected) in which the University Hospital Virgen Macarena participated. The other participating centers have granted authorization to carry out the analysis for the FEN-FENAUREUS project.

Secondary Objectives 3 and 4: This will be a multicenter prospective cohort study. Each patient who develops *S. aureus* bacteremia will be assigned a phenotype and will be followed for 6 months to evaluate differences in mortality and development of complicated bacteremia according to phenotype.

For Secondary Objective 5: This study of genetic (microorganism and the patient), immunological, biochemical and microbiological variables will be performed on representative patients, selected from the prospective cohort (two centers HUVM and HUVV), with the different phenotypes obtained.

Inclusion criteria: adults and children with clinically significant *S. aureus* bacteremia (i.e., associated with at least 2 of the classic criteria for systemic inflammatory response: fever, tachycardia, tachypnea, decreased level of consciousness, hypotension, leukocytosis/leukopenia, or organ failure).

For the study of genetic, immunological, biochemical and microbiological variables in representative patients, a predefined number of patients with each of the phenotypes assigned by the probabilistic model will be randomly selected from the prospective cohort (at the HUV and HUVV).

Exclusion criteria: Non-clinically significant bacteremia; lack of follow-up blood cultures at 48-72 hours; patients who died in the first 48 hours; subsequent episodes in the same patient.

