## **11. Study population and total number of subjects**

For the retrospective study (objectives 1-3) based on the ISAC database, we estimate that we will be able to analyze at least 1,800 cases of SAB that meet the inclusion criteria. Likewise, for objective 4, we estimate that 1,000 cases will be prospectively included from the 14 participating centers during the 34 months of follow-up. For objective 5, given that we estimate that 3 or 4 phenotypes will be identified, 100 patients/ isolates will allow us to include 25-33 per phenotype, which will allow a reasonable number of cases for comparison of microbiological, genetic, endothelial and immunological parameters.

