### Secondary Objectives

- 1 To evaluate the reproducibility of the clinical phenotypes and their correlation with mortality (30 days and 6 months).
- 2 To derive and validate a simplified probabilistic model of clinical phenotype assignment.
- 3 External validation of the simplified probabilistic model of clinical phenotype assignment in a prospective cohort and determination of associations with mortality and the development of complicated bacteremia within 6 months.
- 4 To apply microbiological (clonality testing, genome sequencing), biochemical and immunological techniques to elucidate the pathophysiological and genetic mechanisms underlying the phenotypes.

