## METHODS:

### Design and justification.

This is an entirely observational study.

For the Primary Objective and Secondary Objectives 1 and 2: the ISAC cohort will be analyzed. This cohort is the result of an international study (11 hospitals in 5 countries) on bacteremia caused by *S. aureus* in which the Hospital Virgen Macarena participated (2,590 cases have been collected, and it is estimated that at least 1,800 meet the criteria for inclusion). Authorization to perform the analysis for the FEN-FENAUREUS project has been obtained from the rest of the participating centers.

For Secondary Objectives 3 and 4 a multicenter prospective cohort study will be performed. All patients who develop *S. aureus* bacteremia will be assigned a phenotype and followed for 6 months to evaluate differences in mortality and development of complicated bacteremia between phenotypes.

For Secondary Objective 5 a study of genetic (microorganism and patient), immunological, biochemical and microbiological variables will be performed in representative patients with different phenotypes; these patients will be selected from the prospective cohort at two centers (HUVV and HUVV).

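### The check on the held-out third of ISAC is under-specified: if those patients are assigned to the derived phenotypes rather than re-clustered, it cannot tell real clusters from none

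*Combined protocol and SAP*

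**What the plan says.** Secondary objective 1 is "To evaluate the reproducibility of these clinical phenotypes and their correlation with mortality (30 days and 6 months" (Protocol summary; repeated under General and specific objectives). The method is in Methods, 8. Data analysis, which counts the primary objective as objective 1, so that its ISAC paragraph on objectives 1 and 2 covers secondary objective 1.

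- Derivation: "a two-step cluster analysis with silhouette analysis will be performed on a randomly selected subcohort including two-thirds of the patients".
- Check: "The distribution of phenotypes and characteristics will be validated on the other subcohort with one-third of the patients".
- Size: "we estimate that we will be able to analyze at least 1,800 cases of SAB" (Protocol summary, 11).
- Number of groups: "given that we estimate that 3 or 4 phenotypes will be identified" (same section).

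Both parts come from one cohort, collected in 11 hospitals in 5 countries (Protocol summary, 8. Design).

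The plan does not state how a held-out patient receives a phenotype. It names no patient-level agreement statistic, stability measure, comparison with a one-cluster solution or criterion for success. Silhouette analysis belongs to the derivation step and has no cut-off. In the prospective cohort, each patient's phenotype is calculated from the simplified probabilistic model.

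**The concern.** A clustering algorithm asked for three groups returns three groups, whether the data contain clusters or a continuum. A reproducibility check has to separate these cases. Comparing group shares and average profiles between two random parts of one cohort does so poorly, and not at all if the held-out patients are placed by the rule learned on the first part. That rule cuts the same population in the same place, so shares and profiles agree by construction.

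The phenotypes feed everything later: the assignment model, the comparison of outcomes in about 1,000 prospective cases, and the 100-patient laboratory substudy. Phenotypes that are arbitrary cuts of a continuum could be declared reproducible at the first step and carried through all of these. Because the sentence can be read two ways, the analyst could also choose the reading after seeing the data.

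**Working it through.** The plan states no power, threshold or pass rule for this check, so there is no figure of its own to reproduce. The question is how often the described comparison would look successful with and without clusters.

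**Inputs from the plan.** 1,800 cases; 1,800 × 2/3 = 1,200 for derivation and 600 held out; three groups (the plan expects 3 or 4).

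**Assumptions.** 30 standardised variables; k-means in place of two-step clustering; a pass means chi-square p > 0.05 for phenotype shares between the two parts and a correlation above 0.9 between the two sets of phenotype profiles.

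**Expected result under assignment.** Two random parts cut by one rule have the same expected shares, so a 5% chi-square test should be non-significant in about 1 − 0.05 = 95% of cases, whatever the structure of the data.

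**Simulation (200 runs per row; ARI = adjusted Rand index between independent re-clustering of the third and the labels from the derivation rule).**

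| Data | Assigned: pass | Re-clustered: pass | Median ARI | ARI > 0.8 |
|---|---|---|---|---|
| No clusters, independent variables | 97% | 0% | 0.02 | 0% |
| No clusters, one severity factor | 97% | 61% | 0.85 | 61% |
| No clusters, three correlated factors | 96% | 26% | 0.42 | 10% |
| No clusters, one factor, 15 binary variables | 94% | 62% | 0.83 | 57% |
| Three true clusters | 95% | 94% | 0.995 | 100% |

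Under assignment, 4–5% of variable comparisons within a phenotype differed at p < 0.05 in every row, which is the chance rate. A second set of 60 runs per structure gave passes of 90–98% without clusters against 97% with them (assigned) and 0–58% without clusters (re-clustered). Its median ARI was 0.25–0.82 for correlated data without clusters.

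**Sensitivity to the pass rule.** If each phenotype's own profile must correlate above 0.9 (100 runs), passes under assignment are 84%, 0%, 24% and 0% for the four cluster-free rows and 93% for true clusters. The zeros arise because the middle group of a gradient lies near the overall mean, so its profile is mostly noise. A real cluster lying at the overall mean would fail for the same reason. The result thus depends on a criterion that the plan leaves open.

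**Silhouette (100 runs).** The median was 0.02–0.10 without clusters and 0.14 with three true clusters. With two groups imposed on the one-factor data it was 0.17. Without a cut-off it does not settle the matter.

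**The case against.** **The plan may intend re-clustering.** This is the strongest reply. The sentence allows it, and independent cluster-free data then fail every time. A reader might infer that the check passes on any data without clusters; the documents do not support that, because they leave the method open. But shares and profiles alone still let 26–62% of correlated cluster-free runs through, and clinical variables are correlated.

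**External validation is planned.** Secondary objective 3 uses a prospective cohort from 14 centres. It tests the assignment model and its link with outcome. Because patients are assigned by that model, it does not test whether the groups would re-form. A severity gradient cut at any point could also predict death.

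**An external clustering exists.** Table S7 of the appendix sets a cluster analysis in INSTINCT against portal of entry: (286 + 431 + 409)/1,217 = 92.5% agreement, kappa 0.89. This is relevant, but it is a result and not part of the plan, and the documents do not say whether portal of entry was a clustering input. Its column totals (305/458/454) also differ from the phenotype sizes in Table S8 (243/458/516), with 62 patients moving between A and C; the tables should be reconciled.

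**Leaving out hospitals would be a poor replacement for the split.** This stands. 1,800/11 is about 164 patients per hospital. In a simulation with weakly separated true clusters, median ARI fell from 0.87 at 600 patients to 0.71 at 164 (10th percentile 0.47), so low agreement would partly reflect size. With well-separated clusters the loss was negligible.

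**Phenotype shares.** A reader might take the phenotype C share (1,097/2,128 = 51.6% in ISAC, 516/1,217 = 42.4% in INSTINCT, 329/1,185 = 27.8% in FEN-AUREUS) as proof of instability. It is not. In the appendix the phenotypes follow portal of entry, so the shares reflect case mix, and a reproducible phenotype may differ in prevalence.

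**Conclusion.** The point holds as one of under-specification with a serious consequence under one natural reading. If held-out patients are assigned, the check has no power to distinguish clusters from none under the assumed rule: about 90–98% passes against 95–97%. If they are re-clustered and only shares and profiles are compared, the check discriminates in part, with up to about 60% passes on correlated cluster-free data.

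The assignment result follows largely from the random split and the shared rule. The exact percentages rest on k-means, the assumed variable structures and the assumed pass rule. The low ARI of 0.02 applies only to unrelated variables and should not be read as what re-clustering would show here.

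Using the same 11 hospitals in both parts limits what the check says about other settings, but it is not why cluster-free data pass. Nothing here shows that the phenotypes are unstable; it shows that the planned check might not reveal it if they were.

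**What to change.** Keep the planned two-thirds/one-third split and add to Methods, 8. Data analysis:

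1. The held-out third is clustered independently, blind to the derivation labels.
2. The primary measure of reproducibility is patient-level agreement (adjusted Rand or kappa, with a bootstrap interval) between those clusters and the labels given by the derivation rule.
3. Agreement is judged against a threshold fixed in advance and against a one-cluster reference: data simulated with the observed correlations but no clusters, put through the same procedure. The reference is needed because a single severity gradient can reach an ARI of about 0.8, close to the 0.87 seen with weak true clusters, so a threshold alone may not separate the two.
4. Bootstrap Jaccard stability is reported for each cluster, with case order shuffled because two-step results can depend on it.
5. As a sensitivity analysis only, agreement is reported by left-out country, or by hospital where numbers allow.

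This needs no new data. It costs plan text and computing time, and the stated reproducibility may turn out lower.
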